##### Follow-up

Follow-up will end with the earliest of either an ‘event’ or censoring due to the end of registration or death.

### Statistical analysis

For investigating the effects of varenicline use on each outcome (long-term smoking cessation, frequency of GP and hospital attendance, all-cause and cause-specific mortality, primary care diagnosis of respiratory illness, myocardial infarction, depression or anxiety), we will report a conventional multivariable-adjusted Cox regression, propensity score regression and instrumental variable analysis.

#### Analysis 1: Conventional cox regression

In our first analysis, a conventional observational analysis, we will estimate HRs of the outcomes using Cox-proportional hazards models and the actual prescriptions issued to the patients.^29^ Each patient's date of entry into the cohort will be the date they were first prescribed a smoking cessation therapy. The date of exit for each outcome will be the date on which they first have an event, or are censored due to end of follow-up or death or leaving the practice. We will report these associations adjusted for basic confounders (age and gender), and results adjusted for all measured covariates described above.

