**Methods:**

In this project we will investigate the effects of varenicline compared to nicotine replacement therapies on: (1) long-term smoking cessation and whether these effects differ by area level deprivation; and (2) the following clinically-important outcomes: rate of general practice and hospital attendance; all-cause mortality and death due to diseases of the respiratory system and cardiovascular disease; and a primary care diagnosis of respiratory illness, myocardial infarction or depression and anxiety. The study is based on a cohort of patients prescribed these smoking cessation medications from the Clinical Practice Research Datalink (CPRD). We will use three methods to overcome confounding: multivariable adjusted Cox regression, propensity score matched Cox regression, and instrumental variable regression. The total expected sample size for analysis will be at least 180 000. Follow-up will end with the earliest of either an ‘event’ or censoring due to the end of registration or death.

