### Power calculations

The following power calculations are based on effect sizes and CIs observed in our previously published results, which used data from 110 000 individuals prescribed either varenicline or nicotine replacement therapy.^13^ Based on the rate of 18 000 new prescriptions per year observed in the CPRD from 2006 to 2011,^13^ we estimate that with a further 4 years of follow-up the number of patients prescribed either varenicline or nicotine replacement therapy will have increased by 72 000. Therefore the total expected sample size for analysis will be around 180 000.

In our previous analysis using CPRD data the age-adjusted and sex-adjusted HR for self-harm/suicide for varenicline versus nicotine replacement therapy at 9 months was 0.73 (95% CI 0.54 to 0.99); after adjusting for possible confounders this became 0.90 (95% CI: 0.66 to 1.22).^13^ A 70% increase in sample size would lead to a reduction of the SE by a factor of 1.3, reducing the breadth of the above CI in the adjusted analysis from 0.56 to 0.43.

Rare outcomes, such as self-harm and suicide were used in previous analyses; in this project we will have greater power to explore more common outcome measures. For example, in the previous analysis the 9-month age-adjusted and sex-adjusted HR for all-cause mortality 9 months after first prescription for varenicline versus nicotine replacement therapy was 0.43 (95% CI 0.35 to 0.53); after controlling for possible confounders this became 0.49 (95% CI 0.40 to 0.61). A 70% increase in sample size would lead to a reduction of the SE by a factor of 1.3, reducing the breadth of the above CI in the adjusted analysis from 0.21 to 0.16.

For the effects of varenicline versus nicotine replacement therapy on all-cause mortality, instrumental variable analysis found a risk difference of 0.7 (95% CI −3.3 to 4.7) per 1000 patients treated after 9 months. We estimate that a 70% increase in sample size would narrow the CIs from 8.0 to 6.2.

Using data from our previous project, within 2 years of first prescription, we found 2517 admissions for respiratory disease among 1374 patients; 3144 admissions for cardiovascular disease among 1022 patients; and 3277 admissions for depression or anxiety among 213 patients. This is more events than we found for suicide and self-harm in our previous study; therefore we believe that there will be enough events for this analysis.

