### Data collection and linkage

We will use linked Hospital Episodes Statistics (HES) and ONS mortality data to define frequency of GP and hospital attendance, frequency of all-cause and cause-specific hospitalisation and all-cause and cause-specific mortality. We will test these hypotheses using data from GP practices linked to external data sets only.

These are important hard outcomes for our study. We have already established that for certain outcomes, such as cause specific mortality the linked ONS data are more accurate.^18^ While it is possible to investigate these outcomes using CPRD data from GPs, the data are less precise and consistently recorded.^18^ Thus analyses using linked data are likely to be more precise. Furthermore, the linked data provide direct evidence about secondary care attendance of patients via the HES data. Again, while there are some data about referrals to secondary care in the main tables of the CPRD, the data are not as comprehensive as HES data. Our outcomes of interest occur after September 2006; therefore, we believe that the linked HES and ONS data will provide sufficient coverage for these outcomes.

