##### Outcome 2: Frequency of GP and hospital attendance

We will define service use as the number of visits to GP and hospitals in the 3, 6, 9, 12, 24 and 48 months after first prescription. We will define GP appointments using the clinical data file of the CPRD. This includes all the diagnoses and symptoms that GPs record about all of their patients. As with the other outcomes, the vast majority of diagnoses and symptoms include the date on which the data were added to the database. We will use these dates to calculate the number of times each patient attends primary care. We will define the hospital visits outcome using the linked HES data. We will investigate all-cause hospitalisation and three specific causes of hospitalisation: (1) diseases of respiratory system (ICD-10=J00-J99), (2) cardiovascular disease (ICD-10=I00-I52) and (3) anxiety and depression (ICD-10=F31.3, F31.4, F31.5, F32, F40-F48). Causes of hospitalisation are available for approximately half of the sample. Again these data contain the date on which the event occurred, which we will use to define attendance to secondary care within 3, 6, 9, 12, 24 and 48 months after first prescription.

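### Service use is defined as a number of visits, but Analyses 1 and 2 model time to the first visit, so they do not estimate frequency

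*Protocol article*

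**What the plan says.** Outcome 2 is introduced as a count over fixed windows: "We will define service use as the number of visits to GP and hospitals in the 3, 6, 9, 12, 24 and 48 months" from first prescription. For primary care the derivation is explicit: "We will use these dates to calculate the number of times each patient attends primary care". Other sections use the same idea under other names. The abstract speaks of the "rate of general practice and hospital attendance", and Data collection and linkage says the linked data will "define frequency of GP and hospital attendance, frequency of all-cause and cause-specific hospitalisation".

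The Statistical analysis section gives one list of outcomes for all three methods, and it includes "frequency of GP and hospital attendance, all-cause and cause-specific mortality, primary care diagnosis of respiratory illness". Analysis 1 reports hazard ratios from Cox models with the exit rule "The date of exit for each outcome will be the date on which they first have an event", or at censoring. Analysis 2 fits Cox models to the matched sample with the same entry and exit dates. The Follow-up section also ends observation at an event. Analysis 3 uses additive structural mean models and names a risk difference as its result. Its sentence on time windows covers the adverse event outcomes only. The article contains no count, rate or recurrent-event model.

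**The concern.** A Cox model that removes each patient at the first event estimates the relative hazard of that event. It carries no information on how many visits follow. The effect on NHS service use is one of the stated study aims, and the reason given for it is the cost that smoking places on health services. That cost depends on the volume of visits, not on the date of the first.

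A therapy that changed repeat attendance but left the first attendance unchanged would give a hazard ratio of 1 in two of the three analyses. For GP contacts there is a further difficulty: if most patients return fairly soon for any reason, the first contact mainly reflects timing in the early months and says little about use over 48 months.

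**Working it through.** **1. The plan's own figures.** The article gives no precision or power figure for a service-use effect. Its general projections reproduce: 110 000 + 4 × 18 000 = 182 000, against a stated figure of around 180 000; √1.7 = 1.30; and 0.56 / 1.3 = 0.43, as stated. For admissions it gives only event and patient numbers from the earlier project within 2 years, for example "3277 admissions for depression or anxiety among 213 patients".

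**2. Outcome against model.**
- Outcome 2, GP part: number of attendances per patient in each window.
- Outcome 2, hospital part: opens as a number of visits, but closes by using dates to define attendance within each window, which could mean any attendance in the window.
- Analyses 1 and 2: hazard ratio for the first attendance.
- Analysis 3: risk difference; not stated whether the dependent variable is a count or an indicator.

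**3. Scale of recurrence** (Power calculations section). Admissions per admitted patient = admissions / patients. Share used by a first-event model = patients / admissions.

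| Cause | Admissions | Patients | Per patient | Used | Not used |
|---|---|---|---|---|---|
| Respiratory | 2517 | 1374 | 1.83 | 54.6% | 45.4% |
| Cardiovascular | 3144 | 1022 | 3.08 | 32.5% | 67.5% |
| Depression or anxiety | 3277 | 213 | 15.4 | 6.5% | 93.5% |

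Summed over causes, 1374 + 1022 + 213 = 2609 of 2517 + 3144 + 3277 = 8938 admissions are used, or 29.2%. A patient admitted for two causes counts twice in this sum.

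**4. What a first-event model can miss (assumed scenario, not in the documents).** Let both groups have the same hazard of first admission, and let one have half as many repeat admissions. With m admissions per admitted patient, the ratio of totals is [1 + 0.5(m − 1)] / m:
- m = 1.83: 1.415 / 1.83 = 0.77
- m = 3.08: 2.04 / 3.08 = 0.66
- m = 15.4: 8.2 / 15.4 = 0.53

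The first-event hazard ratio is 1 in all three cases.

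**5. GP visits (assumed rates; the article gives none).** If visits follow a Poisson process at rate r per year, the share with a first visit by 12 months is 1 − exp(−r). For r = 2 this is 86%; for r = 12 it is almost 100%. If rates vary strongly between patients (gamma with shape 1), the share is 1 − 1/(1 + r): 67% for r = 2 and 92% for r = 12. Either way, most patients leave the risk set well before the 48-month horizon.

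**The case against.** The best defence concerns hospital attendance. The closing sentence of Outcome 2 can be read as occurrence within a window, which suits both a first-event model and a risk difference. Time to first admission is also a legitimate question. This stands: for hospital visits the plan is ambiguous rather than plainly contradictory. It does not help the GP part, which is explicitly a number of attendances.

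Three stronger readings are tempting, and the documents do not support them.
- A reader might infer that the plan cannot answer the frequency question at all. Analysis 3 leaves this open: an additive model can take a count and return a mean difference, although the article promises risk differences.
- A reader might infer that the Cox results clash with an instrumental variable analysis of counts. No such analysis is stated. Hazard ratios and risk differences are also on different scales for every outcome here.
- A reader might take 93.5% of admissions unused as 93.5% of information lost. At 15.4 admissions per patient the repeats are strongly clustered, and the number of patients with any event remains 213.

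The admission figures are also cause-specific and limited to 2 years, and the GP illustration rests on assumed rates. Finally, a count model is not the only repair: a recurrent-event model, or redefining the outcome as time to first attendance, would also reconcile the sections. The last of these would give up the question on volume of use.

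**Conclusion.** The point holds for Outcome 2 in Analyses 1 and 2. As written, two of the three analyses estimate time to first attendance, while the outcome is defined as a number of visits. This is not detail left to an analysis plan, because the article assigns Cox regression to attendance frequency by name and fixes the exit rule for each outcome. The mismatch is definite for GP attendance. For hospital attendance the authors must first say whether they mean a count or an occurrence.

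The plan's earlier data show that recurrence is substantial, at 1.8 to 15.4 admissions per admitted patient, so the two quantities could differ materially. How far they would differ between treatment groups cannot be derived from the article. Mortality, incident diagnosis and abstinence are not affected by this point.

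**What to change.** For Outcome 2:
- In Analyses 1 and 2, replace the first-event Cox model with a count or recurrent-event model for each window. Examples are negative binomial, or Poisson with robust variance, with log observed person-time as offset, the same covariates or matched sample, and practice-clustered standard errors.
- In Analysis 3, fit the additive model to the same count or rate and report a mean difference.
- State in Outcome 2 whether hospital attendance is a count or an occurrence, and exempt the count outcome from the rule that ends follow-up at an event.
- State that the rate is while alive and registered. The earlier adjusted mortality hazard ratio was 0.49 (95% CI 0.40 to 0.61), so observed time may differ between groups, and a rate while alive is not the same as a total over 48 months.
- Keep time to first hospital admission, if wanted, as a labelled secondary analysis.

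The cost is revised wording, a different model command and slightly more analysis work, with no new data. Robust variance is needed because a few patients contribute many admissions.

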#### Analysis 2: Propensity score regression

In our second analysis we will construct a sample of patients balanced on covariates and risk factors using a propensity score.^30–33^ We will construct propensity scores using a logistic regression of the actual treatment received on the covariates described above. Therefore, each participant's propensity score will be their conditional probability (odds) of receiving varenicline versus nicotine replacement therapy. We will match each patient receiving varenicline to another patient receiving nicotine replacement therapy with the closest propensity score on a ratio of 1:1 using a nearest neighbour algorithm with no replacement, and matching will be restricted to the common support region. Patients outside the common support region are those prescribed varenicline with propensity scores higher than any patient prescribed nicotine replacement therapy and vice-versa. We will estimate HRs of the outcomes using the propensity score matched sample using Cox regressions using the same entry and exit information as the conventional Cox regression analysis described above.

#### Analysis 3: Instrumental variable analysis

In our third analysis, we will estimate the effects of smoking cessation therapies on the outcomes using physicians’ prescribing preferences as instruments for the prescriptions the GPs issue to their patients. We cannot directly measure the physicians’ preferences; therefore, we will use the prescriptions they issued to their previous patients as a proxy for their preferences. For example, if the instrument was based on just one previous prescription, physicians who previously prescribed varenicline would be categorised as a varenicline prescriber. As with our previous studies we will use seven prior prescriptions to improve the strength of the instruments.^13^
^34^
^35^ Using multiple prior prescriptions will maximise power. We will report risk differences in the outcomes using additive structural mean models estimated via the generalised method of moments.^36–38^

We will categorise each of the adverse event outcomes as occurring within 3, 6, 9, 12, 24 and 48 months of first prescription. We will do this because methods for conducting survival analysis using instrumental variables are not well developed. We will use Stata 13.1 SE to generate all results. The instrumental variable analysis will be conducted using the ivreg2 command and psmatch2 will be used to construct the propensity score.^31^
^39^
^40^ All SEs will be estimated using cluster robust SEs, which account for clustering of patients within practices.

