### Data analysis

#### Exposure measures

First time users of the smoking cessation therapies (varenicline or nicotine replacement therapy) will be defined as people who received at least one prescription of the product after the 1 September 2006 but with no use of a related product during the 12 months before the index date (the first date on which a prescription was issued). Langley *et al*^19^ found the smoking cessation prescription data in the THIN database, which is closely related to the CPRD, to be highly comparable to national dispensing data. The prescriptions will be defined by the therapy file in the CPRD, which contains a list of all prescriptions issued to patients by their GP. Each therapy record records the date a prescription was issued, the quantity of drug prescribed and the dose.

The primary analysis will be limited to the first treatment episode. This is analogous to an intention-to-treat analysis in a RCT.^20^ This ensures that the target parameter estimated in the observational study will be comparable to the parameter estimated by a RCT. For example, if patients’ treatment adherence and duration is related to whether they experience adverse events, then definitions of exposure which are based on treatment adherence may provide unreliable evidence of the causal effect of the prescription on adverse outcomes. This analysis framework was described in Hernán *et al* (2008). The intuition is that most randomised trials recruit individuals and then split participants into different treatment arms. This means that comparison groups are implicitly from first treatment. The primary analysis in an RCT typically reports an intention to treat estimate, which is the difference in allocation between arms of the trial based on allocation, rather than the treatment the participant received. To obtain results that are comparable to a randomised trial Hernán argued that analysts need to construct cohorts that also follow-up patients from first treatment, rather using retrospectively defined exposures (eg, retrospectively defining exposure as ever exposed to varenicline).

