To mimic an intention-to-treat analysis in an RCT, in our primary analysis patients who are initially prescribed nicotine replacement therapy, but later switch to varenicline, will be allocated to nicotine replacement therapy and vice-versa. We will use an intention-to-treat design for two reasons. First, while there are theoretical statistical models for estimating the effects of treatment switching such as marginal structural models, these methods require the strong assumption that there are no unmeasured confounders and typically require detailed data on time-varying confounders, which are unlikely to be available in the CPRD. Second, to our knowledge there are no instrumental variable methods to estimate the effects of switching treatment. However, we will investigate the number of participants who switch treatment as a sensitivity analysis.

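### If prescribing preference also steers later switching, the instrumental variable estimate may not be the intention-to-treat effect of the first prescription, and a count of switchers cannot show whether it is

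*Protocol article*

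**What the plan says.** Under Exposure measures, the protocol article states that "The primary analysis will be limited to the first treatment episode" and likens this to intention-to-treat in a trial. It says the choice secures a target parameter comparable to that of a randomised trial. Accordingly, "patients who are initially prescribed nicotine replacement therapy, but later switch to varenicline, will be allocated to nicotine replacement therapy and vice-versa". One of the two reasons given is that "to our knowledge there are no instrumental variable methods to estimate the effects of switching treatment". The planned check is that "we will investigate the number of participants who switch treatment as a sensitivity analysis".

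Under Analysis 3, the effects are estimated "using physicians’ prescribing preferences as instruments for the prescriptions the GPs issue to their patients". Preference is not observed, so "we will use the prescriptions they issued to their previous patients as a proxy for their preferences", and "we will use seven prior prescriptions to improve the strength of the instruments". On the estimator: "We will report risk differences in the outcomes using additive structural mean models estimated via the generalised method of moments". Outcomes are classified at 3, 6, 9, 12, 24 and 48 months after the first prescription.

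The article gives no switching rate and no first-stage strength. It does not discuss whether a physician's preference also acts on prescriptions after the first.

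**The concern.** In a trial, the randomisation list has no say in later prescribing except through the arm it assigned. A physician's preference is different, because it is still there at the next consultation. A physician who favours varenicline may be more ready to move a patient from nicotine replacement to varenicline, and less ready to do the reverse. Any such influence is a path from instrument to outcome that bypasses the modelled exposure.

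The intention-to-treat rule does not close this path for the IV analysis. Switching that follows from the first prescription itself belongs to the intention-to-treat effect and does no harm. Switching driven directly by preference does not belong to it, yet the estimator credits its effect to the first prescription. A single count of switchers mixes the two kinds. What matters is whether switching differs by level of the instrument.

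At stake is the meaning of one of the three planned estimates. The later windows are more exposed, since there is more room to switch by 24 or 48 months than by 3.

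**Working it through.** **The plan's own IV figure.** The only IV figures are in Power calculations: a mortality risk difference of 0.7 per 1000 (95% CI −3.3 to 4.7, width 8.0), with the width projected to fall to 6.2. Expected size is 110 000 + 4 × 18 000 = 182 000. Then 8.0/√(182/110) = 8.0/1.286 = 6.22, and 8.0/1.3 = 6.15. The figure reproduces. It concerns random error only and says nothing about the exclusion restriction.

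**General form.** Let X1 be the first prescription, X2 the later treatment and Z the instrument, with X2 = a + φX1 + γZ and outcome effects b1 (first) and b2 (later). Let π be the first-stage difference.

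- Intention-to-treat effect of the first prescription = b1 + b2φ
- IV estimand = b1 + b2φ + b2γ/π
- Bias = b2γ/π

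φ is switching caused by the first prescription and appears in both lines. Only γ, the direct effect of preference on later treatment, separates them.

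**Illustration (all inputs assumed).** High- and low-preference physicians start varenicline in xH = 45% and xL = 15% of patients, so π = 0.30. Patients starting nicotine replacement later switch to varenicline at rates sH and sL. Varenicline has the same effect b whether started or switched to.

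- IV/b = [(xH + (1 − xH)sH) − (xL + (1 − xL)sL)]/(xH − xL)
- First-prescription effect/b = 1 − mean of sH and sL

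| sH / sL | IV/b | First-prescription effect/b | Ratio |
|---|---|---|---|
| 20% / 20% | (0.560 − 0.320)/0.30 = 0.80 | 0.80 | 1.00 |
| 10% / 8% | (0.505 − 0.218)/0.30 = 0.957 | 0.91 | 1.05 |
| 15% / 5% | (0.5325 − 0.1925)/0.30 = 1.13 | 0.90 | 1.26 |
| 30% / 10% | (0.615 − 0.235)/0.30 = 1.27 | 0.80 | 1.58 |

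This agrees with the general form. For 30%/10%, the average direct effect is γ = 0.70 × 0.20 = 0.14, so γ/π = 0.467 and 0.80 + 0.467 = 1.27.

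**Dependence on the later effect (30%/10%).** If later varenicline has half the effect, IV/b = (0.30 + 0.5 × 0.08)/0.30 = 1.13 against 1 − 0.5 × 0.20 = 0.90, a ratio of 1.26. If it has no effect on the windowed outcome, both equal b and there is no bias.

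**Direction.** In simulations with 182 000 patients, 100 replicates and π = 0.30 (Monte Carlo standard error about 0.25 per 1000), IV against the intention-to-treat effect, per 1000, was:

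- switching unrelated to preference: −8.3 against −8.0 (no bias beyond simulation error)
- switching towards the preferred drug, later effect of the same sign: −11.1 against −8.0 (inflated)
- the same switching, later effect of opposite sign: −9.1 against −11.0 (attenuated)
- switching away from the preferred drug, same sign: −4.3 against −8.0 (attenuated)
- no drug effect at all: 0.1 against 0 (null preserved)

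**The case against.** A reader might infer that the design necessarily breaks the exclusion restriction and inflates the estimate. The article does not support that. It neither states nor quantifies a direct effect of preference on later prescribing, and the sign of the bias depends on two unknowns. The larger figures above rest on threefold differences in switching and on a later effect as large as the initial one. A modest difference gives about 5%. Outcomes are cumulative from the first prescription, so a switch after an event cannot affect it. For abstinence, any later current-smoker record counts as relapse under Outcome 1, which partly closes the path for that outcome. All of this stands.

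A reader might also infer that a gap between the Cox and IV results will be taken as confounding removed. The article says only that methods with distinct assumptions will be triangulated. The Cox analyses give hazard ratios and the IV analysis gives risk differences, so no direct numerical comparison is planned.

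Re-running the IV model with any varenicline use as exposure is not a clean remedy. It comes close to the ever-exposed definition that Exposure measures argues against. If later varenicline has no effect on the outcome (30%/10% case), it returns 0.30/0.38 = 0.79b where the planned model is unbiased.

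Finally, a condensed article may leave the layout of a switching table to a fuller document, and it does not say that the count will be overall only. That is fair as to detail. It does not answer the main point: the article presents the first-prescription rule as securing a trial-like parameter, and for a preference instrument that does not follow without a further assumption about switching.

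**Conclusion.** The concern holds conditionally. With a preference instrument and exposure fixed at the first prescription, the IV risk difference equals the intention-to-treat effect only if preference does not act on later treatment except through the first prescription, or if later treatment does not affect the outcome. If neither holds, the bias is b2γ/π. Inflation is the likelier direction, since switching towards the physician's preferred drug is the natural pattern, but attenuation is possible and a true null for both drugs is preserved.

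No size can be derived from the article. Under the assumed 45%/15% first stage and an equal later effect, the overstatement runs from nil (equal switching), through about 5% (10% versus 8%), to 58% (30% versus 10%). It shrinks as the later effect shrinks. The 3-month window has the least room for it and the 24- and 48-month windows the most. A count of switchers not split by instrument level cannot tell these cases apart.

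**What to change.** Replace the simple count of switchers under Exposure measures with a table of switching in each direction by level of the instrument, within each horizon, counting only switches made before the event. State the exclusion restriction as it applies to a first-prescription exposure.

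Where switching varies with the instrument:

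- do not label the IV estimate the intention-to-treat effect
- give more weight to the shorter windows
- report how far the estimate moves, using b2γ/π, over a plausible range of γ and b2

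An IV model with any varenicline by the horizon as exposure may be shown as a secondary sensitivity analysis only, with its assumption of a timing-invariant effect stated.

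The cost is one table and a simple sensitivity calculation per outcome and horizon. The therapy file already holds the date of every prescription the GP issued.
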